#### Mortality

Number of deaths will be extracted from the participant’s medical record. Time and cause of each death will also be extracted (an outcome measure only in phase 2).

### Sample size

Sample size calculations have been made to ensure that we have a sufficient sample size to detect difference in change in all three primary outcomes for both Phase 1 and 2. For these a priori power calculations, the sample size has been determined assuming a two-sided alpha level of 0.05 and 80% power.

### Phase 1

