### Primary outcomes

Phase 1 and phase 2 include the same three primary outcomes. These are multiple primary outcomes and not co-primary outcomes. Each outcome is deemed sufficient on its own to establish intervention efficacy. Multiple primary outcomes are selected in the COPD-HIIT project as we intend to determine the effects on multiple extrapulmonary manifestations of the disease which cannot be adequately quantified using a single primary outcome [61–63].

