#### Cognitive function

Assuming an SD of 0.4, a total sample size of 60 individuals (30 per group) is needed to detect a relevant difference of 0.27 in a global cognition z-score measured using a cognitive test battery [118]. A change in *z*-score of 0.27 is clinically relevant associated with increased all-cause, respiratory, and cardiovascular mortality. To account for a drop-out rate of approximately 15% at 3 months, a total of 70 participants is necessary.

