### Statistical methods

The change-from-baseline analyses will be performed after the last participant has completed all assessments of phase 1 and phase 2, respectively, after monitoring and data quality checks. Analyses will be performed blinded by the investigators supported by a biostatistician. All statistical tests will be conducted as two-sided, with the alpha level set at 0.05.

Baseline variables and descriptive statistics with continuous data will be presented with mean (SD) or median (IQR) as appropriate. Continuous data with normative values (for example, VO_2_peak and lung function values) will also be presented as % predicted value. Ordinal variables will be presented as median (IQR) or as *n* (%), and categorical variables will be presented as *n* (%).

A separate detailed SAP with further details about the statistical analyses including the method to handle family-wise error rate for the multiple primary outcomes will be published and finalized before the database is locked and randomization codes unblinded. In line with recommendations, it increases transparency and replicability and might be updated in response to new methods, challenges encountered during the trial, funding availabilities, and emerging evidence during the period of the trial [130, 131].

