#### Statistical methods—outcomes

For primary and secondary outcomes with continuous data, treatment effect will be estimated by mean change-from-baseline (delta-value (Δ)) with 95% confidence intervals and the effect size (ES). The between-group effects will be analysed using analysis of covariance (ANCOVA). In the ANCOVA, baseline values, age, sex, centre, and VO_2_peak will be used as covariates. In phase 1, the primary analyses will be one model for the COPD group and one model for HC. In addition, to investigate any differential effects to the interventions between COPD and HC, a two-way ANCOVA including the Group (COPD/HC) × Intervention (supramaximal HIIT/MICT) interaction will be performed. In phase 2, there will be one model with the three arms (supramaximal HIIT, MICT, and usual care). Additional details will be provided in the SAP.

The assumptions of linearity, normality of residuals, and homogenous variance will be checked using residual plots, normal quantile plots, and histograms. Violations of linearity and normality assumptions will be dealt with by transformations of the dependent variable or non-linear modelling of the independent variables. Outliers will not be removed unless there is a methodological reason for it.

Feasibility of intervention outcomes and number of responders will be described with descriptive statistics and analysed with between group (HIIT/MICT) comparisons in both the COPD (phase 1 and 2) and HC group (phase 1).

In phase 1, hospitalization and exacerbations during the intervention will be presented descriptively. In phase 2, mortality, hospitalizations, and exacerbations will be presented with descriptive statistics and analysed using Kaplan–Meier curves and Cox proportional hazard models.

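### The 80% power claimed for all three primary outcomes is calculated at an unadjusted 0.05, with no allowance for the family-wise control that the protocol promises

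*Protocol article*

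**What the plan says.** The Sample size section states its aim as a "sufficient sample size to detect difference in change in all three primary outcomes for both Phase 1 and 2". It adds that "the sample size has been determined assuming a two-sided alpha level of 0.05 and 80% power".

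Under Primary outcomes, the three outcomes are described as multiple rather than co-primary: "Each outcome is deemed sufficient on its own to establish intervention efficacy".

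Statistical methods says "All statistical tests will be conducted as two-sided, with the alpha level set at 0.05". It also says that the SAP will give further details, "including the method to handle family-wise error rate for the multiple primary outcomes".

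The sample-size subsections and the text on covariates mention no split of alpha. Under Phase 2 of the Sample size section, the increase from 70 to 92 participants with COPD in phase 1 is put down to uncertainty about the SD. The 46 per arm in phase 2 is put down to further drop-out, with a reference back to the two-group phase 1 calculation. Statistical methods—outcomes gives phase 1 two primary models, one in COPD and one in healthy controls, and phase 2 a single three-arm model.

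**The concern.** When any one of three outcomes can establish efficacy, the false-positive rate must be controlled across the three, and the protocol accepts this. Such control has a price in per-outcome power. Bonferroni tests each outcome at 0.0167. Holm starts at 0.0167 and relaxes only after a rejection. A fixed sequence gives 0.05 to the first outcome, and the later ones are tested only if the earlier ones succeed. No procedure gives all three an unconditional 0.05, yet the sizing assumes exactly that.

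The margin between 70 and 92 is already assigned to SD uncertainty, so it cannot also pay for multiplicity. At stake is whether the stated 80% for each of the three outcomes describes the trial that will be analysed. The planned blinded re-estimation in phase 2 is affected too: at an unadjusted alpha it would re-size to the wrong target.

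**Working it through.** **Inputs (Sample size section).** Standardised differences:
- Cognition: 0.27/0.4 = 0.675
- Quadriceps power: 19.4/26.8 = 0.724
- VO2: 3.5/4.6 = 0.761

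Testing is two-sided with 1:1 allocation. The protocol says covariate gains were not used in the sizing, so none is used here.

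**The plan's own figures.** With n per group = 2 × ((z for alpha + z for power)/d)² at 0.05 and 80%, (1.960 + 0.842)² = 7.849.
- Cognition: 2 × 7.849/0.675² = 34.5, so 35 (36 by t-test). The plan states 30 per group: "Assuming an SD of 0.4, a total sample size of 60 individuals (30 per group) is needed to detect a relevant difference of 0.27". Power at 30 is 73% by t-test (74% by normal approximation).
- Quadriceps power: 30.0, so 30 (31 by t-test). The plan states 30.
- VO2: 27.1, so 28 (29 by t-test). The plan states 26.

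The cognition figure is therefore short at plain 0.05, before multiplicity enters.

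**Evaluable numbers per arm.**
- COPD phase 1: 46 × 0.85 = 39
- Healthy controls: 35 × 0.85 = 30
- Phase 2: 46 × 0.70 = 32 if the 30% drop-out is the whole loss, or 46 × 0.85 × 0.70 = 27 if it comes on top of the 15%. The text allows both, so this range is an assumption.

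**Power by two-sample t-test, cognition / quadriceps / VO2.**

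| Setting | Per arm | Alpha 0.05 | Alpha 0.05/3 = 0.0167 |
|---|---|---|---|
| COPD phase 1 | 39 | 84 / 88 / 91% | 70 / 77 / 82% |
| Healthy controls | 30 | 73 / 79 / 83% | 56 / 63 / 68% |
| Phase 2, upper | 32 | 76 / 81 / 85% | 60 / 67 / 72% |
| Phase 2, lower | 27 | 68 / 74 / 78% | 51 / 58 / 63% |

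The normal approximation gives figures up to about three points higher. For 80% at 0.0167 the evaluable n per arm is 48/42/38 by t-test (46/40/37 by normal approximation).

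**What other procedures and success rules give.** These come from 400,000 simulated correlated normal test statistics. Outcome correlations of 0, 0.3 and 0.6 are assumed, because the protocol gives none.
- Holm, all three effects real: 81–90% per outcome at 39 per arm and 68–79% at 30.
- Holm, only the cognition effect real: cognition has 72% at 39 per arm and 59% at 30.
- Bonferroni, at least one outcome significant, all effects real: 99/97/93% at 39 per arm and 96/91/85% at 30 (correlation 0/0.3/0.6). The low end at 27 per arm is about 81%.

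**The case against.** The strongest reply is that the protocol expressly promises "the method to handle family-wise error rate for the multiple primary outcomes" in an SAP to be finalised before unblinding, and that the loss of power depends on the procedure chosen there. This stands. Leaving the method to the SAP is normal, and the figures at 0.0167 are the first-step case, not a forecast. Under Holm with all effects real, COPD phase 1 keeps about 80% or more for every outcome. If success means at least one outcome, power is good throughout when all effects are real. The Sample size section, however, claims power for all three outcomes, and that claim is what fails.

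The analysis is also an ANCOVA, whose gain was left out of the sizing. At 0.0167, cognition would regain 80% if covariates explained about 1 − 39/48 = 19% of the variance in COPD phase 1, or 1 − 30/48 = 38% in healthy controls. The protocol gives no such figures, so this may help but cannot be counted.

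Several stronger readings are tempting, and the documents do not support them.
- A reader might infer that the error rate is uncontrolled, at 1 − 0.95³ = 14% for independent outcomes. The promise of family-wise control rules this out, and the general 0.05 can be read as the family-wise level. It is ambiguous rather than wrong.
- A reader might count nine phase 2 tests, giving 1 − 0.95⁹ = 37% or an alpha of 0.05/9. The plan specifies one three-arm model, not nine unadjusted tests, and pairwise contrasts that share arms are not independent.
- A reader might say the 80% vanishes altogether, or blame multiplicity for the whole shortfall. VO2 in COPD phase 1 stays at 82% even at 0.0167, and cognition at 30 per arm is at 73% with no adjustment.

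**Conclusion.** The point holds as a mismatch between the claimed power and the promised error control. Going from 0.05 to a first-step 0.0167 costs about 9–14 percentage points per outcome in COPD phase 1, 15–17 in healthy controls and 13–17 in phase 2. In healthy controls and phase 2 every outcome then falls below 80%. In COPD phase 1 the loss is modest: cognition falls clearly below 80%, quadriceps power slightly, and VO2 stays above.

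These sizes rest on the protocol's own effects and SDs, the completer numbers derived above, no covariate gain and the first-step alpha. They do not show that the trial is too small for its any-one-outcome success rule if all three effects are real. The blinded phase 2 re-estimation may also change the numbers there.

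**What to change.** - State that 0.05 is the family-wise level over the three primary outcomes within each primary comparison, using for example Holm or Hochberg. The detail can stay in the SAP.
- Restate per-outcome power at the adjusted alpha for the planned evaluable numbers, correcting the cognition figure at the same time. Add the power for at least one outcome if that is the intended success criterion, with the assumed correlations.
- Use the same adjusted alpha in the blinded phase 2 re-estimation.
- For phase 2, say how the three-arm comparisons enter the family, for example an overall test followed by pairwise tests. Usual care need not leave the primary objective. Restricting the primary contrast to the two randomised arms would change the stated question and is not needed for error control.

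The cost is wording in the protocol and SAP and a less favourable stated power. The restatement itself needs no extra participants.

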#### Cognitive function

Assuming an SD of 0.4, a total sample size of 60 individuals (30 per group) is needed to detect a relevant difference of 0.27 in a global cognition z-score measured using a cognitive test battery [118]. A change in *z*-score of 0.27 is clinically relevant associated with increased all-cause, respiratory, and cardiovascular mortality. To account for a drop-out rate of approximately 15% at 3 months, a total of 70 participants is necessary.

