**Methods:**

COPD-HIIT is a prospective, multi-centre, randomized, controlled trial with blinded assessors and data analysts, employing a parallel-group designed trial. In phase 1, we will investigate the effects and mechanisms of a 12-week intervention of supramaximal HIIT compared to MICT in people with COPD (*n* = 92) and matched healthy controls (*n* = 70). Participants will perform watt-based cycling two to three times weekly. In phase 2, we will determine how exercise training and inflammation impact the trajectories of neurodegeneration, in people with COPD, over 24 months. In addition to the 92 participants with COPD performing HIIT or MICT, a usual care group (*n* = 46) is included in phase 2. In both phases, the primary outcomes are a change from baseline in cognitive function, cardiorespiratory fitness, and muscle power. Key secondary outcomes include change from baseline exercise tolerance, brain structure, and function measured by MRI, neuroinflammation measured by PET/CT, systemic inflammation, and intramuscular adaptations. Feasibility of the interventions will be comprehensively investigated.

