#### Muscle power and cardiorespiratory fitness

A sample size of 70 individuals (*n* = 35 per group) is also sufficient to detect a difference of 19.4% (SD 26.8%) [74] in quadriceps power (*n* = 30 per group) and to detect a relevant difference in maximal oxygen consumption (VO_2_max) of 3.5 mL/kg/min (SD 4.6 mL/kg/min) [119] (*n* = 26 per group) measured during a CPET. A difference of 3.5 mL/kg/min is associated with a 15% decrease in risk for cardiovascular disease [120]. No clinically relevant difference exists for muscle power; however, a difference of 19.4% is the minimal detectable change (MDC) from repeated testing of quadriceps peak power in older adults, as calculated by MDC = 1.96 × √2 × standard error of measurement (SEM) [74].

### Phase 2

In total, 138 individuals with COPD will be included in phase 2 (supramaximal HIT (*n* = 46), MICT (*n* = 46), and usual care (*n* = 46)). The sample size is estimated to account for an up to 30% additional drop-out rate at 24 months, in line with previous literature [121–123]. See phase 1 for complete details on the main sample size calculation. Additionally, as reported above in phase 1, the SD of 0.4 in the cognitive test battery is estimated from a trial in healthy adults comparing low to higher-intensity exercises [118] and not in patients with COPD. In phase 1, this uncertainty will be addressed with the increase in sample size from 70 to 92. However, for phase 2, we will instead perform an interim blinded sample re-estimation after half of the participants have performed baseline and 24-month follow-up, using recommended procedures for non-comparative data [124, 125], and adjust the sample size accordingly. These adaptations are recommended when there is any uncertainty in the SD. Importantly, using non-comparative data does not inflate the type I error probability or induce any bias in the treatment effect estimate (as it would if comparative data had been used) [124, 125].

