### Multicentre trial and covariates

The specific trial design is a stratified multicentre trial with individual randomization at each involved centre. Using this design results in a gain in power [126], not a loss in power typical of randomized cluster trials where observations on individuals in the same cluster tend to be correlated. Therefore, no increase in the sample size is necessary even though we collect data at two research centres. In contrast, the sample size could be reduced for a given power [126]. Furthermore, in the statistical analysis (described below), we will adjust the analysis for the predictive covariates age, sex, VO_2_peak, and centre—the latter as appropriate when stratifying the randomization. Adjusting for covariates in the statistical analysis is also associated with a gain in statistical power, or equivalently, a reduced sample size requirement [127–129]. Yet, we have taken a conservative approach and have not accounted for this when estimating the required sample size due to the complex assumptions the calculations require, leading to uncertainty of how much reduction in the required sample size can be expected.

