### Allocation, randomization, and masking

In phase 1, participants will be randomized to either interventional arm or control arm with a 1:1 allocation ratio, using a computer-generated (Sealed Envelope Ltd., London, UK) blocked randomization schedule with varying block sizes of two or four, stratified by sex (male, female) and centre with equal allocation to all trial arms. For phase 2, only the participants with COPD will continue the maintenance program in their allocated group.

Group allocation will be performed after participants have been recruited into the trial; baseline assessments have been completed and eligibility confirmed. The allocation sequence will be kept in an opaque, tamper-proof sealed, and stapled envelope that will be concealed until the end of the outcome assessment. By using aluminium foil inside the envelope, it will be impermeable to intense light. A delegated person independent from enrolment, assessments, and training will generate the allocation sequence, enrol participants, and assign participants to interventions.

Outcome assessors and data analysts will be masked to group allocation. Participants will be instructed not to reveal their group allocation to the outcome assessor during interim-, 12-week, and 24-month trial assessments. In case of failure of keeping the outcome assessor masked, a second outcome assessor will be available. Given the nature of the interventions, neither participants nor instructors of the training sessions can be masked during the intervention. Hypotheses of the trial will not be revealed to the participants during their participation.

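### The Phase 1 cognition sample size does not follow from its printed inputs: 36 per group are needed, not 30, which mainly affects the healthy-control model

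*Protocol article*

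**What the plan says.** The Sample size section of the protocol article sets common design values for all three primary outcomes: "the sample size has been determined assuming a two-sided alpha level of 0.05 and 80% power". The Phase 1 subsections then give one calculation per outcome:

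- Cognition: "Assuming an SD of 0.4, a total sample size of 60 individuals (30 per group) is needed to detect a relevant difference of 0.27". This is then inflated: "To account for a drop-out rate of approximately 15% at 3 months, a total of 70 participants is necessary".
- Quadriceps power: 70 participants are said to be "sufficient to detect a difference of 19.4% (SD 26.8%) [74] in quadriceps power (*n* = 30 per group").
- Cardiorespiratory fitness: a difference "of 3.5 mL/kg/min (SD 4.6 mL/kg/min) [119] (*n* = 26 per group) measured during a CPET".

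Allocation is 1:1 ("participants will be randomized to either interventional arm or control arm with a 1:1 allocation ratio"). The abstract plans Phase 1 "in people with COPD (*n* = 92) and matched healthy controls (*n* = 70"), that is 46 and 35 per arm. The Phase 2 paragraph of the Sample size section explains the rise from 70 to 92 in COPD as the answer to an uncertain SD for the cognitive score, since that SD came from healthy adults. The section on multicentre trial and covariates discusses the power gained by covariate adjustment and then says: "Yet, we have taken a conservative approach and have not accounted for this when estimating the required sample size". Under Statistical methods—outcomes, the primary Phase 1 analyses are two separate models, one for COPD and one for healthy controls.

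**The concern.** All inputs to the cognition calculation are printed, and the printed result is smaller than they imply. Covariate adjustment cannot explain the difference, because the protocol says it took no credit for it. The figure is therefore below the unadjusted requirement, although the approach is described as conservative.

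Two statements depend on it. First, healthy-control enrolment is the cognition figure plus drop-out, with nothing added, and that cohort has its own primary model. If 30 evaluable per arm is too few, the power claimed for cognition in that model is too high. Second, the step from 70 to 92 in COPD is offered as protection against a larger SD than assumed. If 70 was already too small, part of that step repairs the base figure and less protection remains than the text suggests.

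**Working it through.** **Inputs, all from the protocol article.** Two-sided alpha 0.05, power 80%, 1:1 allocation, 15% drop-out at 3 months. Cognition: difference 0.27, SD 0.4. Quadriceps power: 19.4%, SD 26.8%. VO2: 3.5, SD 4.6 mL/kg/min. Enrolment per arm: COPD 46, healthy controls 35.

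**Formula.** With d = difference / SD, the normal approximation is n per group = 2 × ((1.960 + 0.8416) / d)² = 15.70 / d². The two-sample t-test adds about one per group.

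**Attempt to reproduce the stated figures.**

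| Outcome | d | Normal formula | t-test | Stated | t-test power at stated n |
|---|---|---|---|---|---|
| Cognition | 0.27/0.4 = 0.675 | 34.45 → 35 | 35.44 → 36 | 30 | 72.9% |
| Quadriceps power | 19.4/26.8 = 0.724 | 29.96 → 30 | 30.95 → 31 | 30 | 78.7% |
| VO2 | 3.5/4.6 = 0.761 | 27.12 → 28 | 28.11 → 29 | 26 | 76.7% |

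The quadriceps figure reproduces with the normal formula. The VO2 figure is two to three per group short (power at 26 by the normal formula is 78.3%). The cognition figure is five to six short (power at 30 by the normal formula is 74.3%). A one-sided test would give 28 for cognition, which contradicts the stated two-sided alpha and still does not give 30.

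**What would give 30 for cognition.** By the t-test, an SD of about 0.367 with difference 0.27, or a difference of about 0.294 with SD 0.4. By the normal formula, an SD of about 0.37 or a difference of about 0.29. Neither is printed.

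**Corrected enrolment for cognition.** 2 × 36 = 72 evaluable; 72 / 0.85 = 84.7, so 85 enrolled, against the stated 70.

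**Power at planned enrolment after 15% drop-out (t-test, alpha 0.05 per outcome, no covariate adjustment).**

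| Cohort | Evaluable per arm | Cognition | Quadriceps | VO2 |
|---|---|---|---|---|
| Healthy controls | 35 × 0.85 = 29.75, about 30 | 73% | 79% | 83% |
| COPD | 46 × 0.85 = 39.1, about 39 | 84% | 88% | 91% |

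In healthy controls, the standardised difference detectable with 80% power at 30 per arm is 0.736, so the cognition difference is 0.736 × 0.4 = 0.294. With no drop-out at all, 35 per arm gives 79.5%.

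**Margin for a larger SD in COPD.** Of the 92 − 70 = 22 added participants, 85 − 70 = 15 make up the corrected requirement and 7 are left. At 39 per arm the standardised difference detectable with 80% power is 0.643. Power therefore falls below 80% once the SD exceeds 0.27 / 0.643 = 0.42, which is 5% above the assumed 0.4.

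**The case against.** Four objections deserve weight.

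1. *Rounding.* The SD is printed to one decimal, so any value from 0.35 to just under 0.45 would appear as 0.4, and a value near 0.37 gives 30. This stands as a possible explanation. The source trial is not at hand and the protocol does not give the unrounded SD, so it can be neither confirmed nor excluded. It bears on the remedy: the wrong item may be the printed SD rather than the printed n. Either way, the text does not agree with itself.

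2. *The planned analysis is ANCOVA.* The 73% belongs to an unadjusted comparison. The model adjusts for baseline value, age, sex, centre and VO2peak. At 30 per arm, 80% is restored if covariates explain about 16% of the outcome variance: 1 − (0.675/0.736)² = 0.16. This also stands. A reader might infer that the healthy-control model will actually run at 73%, but the documents give no explained variance and do not support that. What adjustment cannot do is account for the stated 30.

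3. *Scope.* A reader might infer that the Phase 1 sample sizes as a whole miss 80% power. They do not. Quadriceps power reproduces, and its 79% in healthy controls is only the gap between the normal formula and the t-test. VO2 reaches about 83% in healthy controls because enrolment was never set by the figure of 26. All three outcomes exceed 80% in COPD.

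4. *Practical effect.* A reader might infer that more participants must be enrolled. Nothing here requires it. For Phase 2 the protocol already plans a blinded re-estimation of the sample size, so no conclusion about Phase 2 power is drawn.

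**Conclusion.** The concern holds for the cognition calculation. From the printed inputs, 36 per group are needed (35 by the normal formula) where the protocol states 30, and 30 per group has about 73% unadjusted power. The material shortfall is in the healthy-control cognition model. The COPD comparison stays above 80% at the assumed SD, but with much less reserve than the move to 92 suggests. The VO2 figure is a small misstatement with no effect on planned power.

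This rests on the printed SD and difference being the values used, on 15% drop-out spread evenly over the arms, and on alpha 0.05 for each outcome as the Sample size section states. How the three primary outcomes share the family-wise error is left to the SAP and is not judged here.

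**What to change.** - Cognition: correct the requirement to 36 per group (72 evaluable, about 85 enrolled with 15% drop-out). If an SD near 0.37 was used, print that SD instead and keep 30.
- VO2: correct 26 to 28 or 29 per group, and name the method, so that all three figures rest on the same formula. With the t-test, quadriceps power becomes 31.
- State what planned enrolment delivers after 15% drop-out, labelled as unadjusted and with a note that covariate adjustment may raise it. With SD 0.4, for cognition, quadriceps power and VO2 in turn: COPD about 84%, 88% and 91%; healthy controls about 73%, 79% and 83%, with a detectable cognition difference of about 0.29. If a smaller SD is printed, recompute the cognition entries.
- Quantify the statement that 92 addresses the SD uncertainty. On the printed inputs it holds 80% power up to an SD of about 0.42.

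The cost is a text correction in the protocol, carried into the SAP. Enrolment, design and analysis do not change. The price is a less favourable power statement for cognition in healthy controls.
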